### Statistical analysis

2.8

In the full analysis set, all randomized patients will be kept in the treatment group to which they were originally randomized. Moreover, patients without protocol deviation will be included in the per protocol set. Patients of the per protocol set will be included in baseline information analysis rather than in primary analysis if the CTO-PCI fails. Patients will not be included in the primary analysis if the MACEs occur.

Continuous variables normally distributed will be presented as means ± standard deviation, and student *t*-test will be used to make comparisons between two independent samples. Median and 4-quintile intervals will be used to express variables that are not normally distributed, and the Mann–Whitney *U*-test will be used to compare differences. Categorical variables will be presented as frequencies and percentages, and the differences between groups will be assessed using a chi-square test. Survival analysis will be performed using a Kaplan–Meier curve and Cox regression analysis. A 2-sided *P*-value < .05 will be considered statistically significant.

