### Treatment groups

2.2

Patients in the CTO-PCI group receive PCI treatment involving both the CTO artery and the non-CTO artery. Patients of the non-CTO PCI group will only have PCI performed on the non-CTO artery. To ensure safety of all patients, they will be monitored, and those with persisting clinical symptoms occurring within one month of OMT will undergo PCI of CTO artery.

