#### Secondary endpoints

2.6.2

Secondary endpoints involve the occurrence of MACEs, defined as all-cause mortality, cardiac death, a first or recurrent, non-fatal, acute myocardial infarction, target lesion revascularization (PCI or CABG), stroke, heart failure and cardiac rehospitalization within 1, 6, and 12 months post-PCI. Other secondary endpoint will include changes in myocardial viability in the territory supplied by the CTO artery between the baseline and 12 months post-PCI, to be determined by CMR. In addition, QOL changes at 1, 6, and 12-month follow-up appointments will be assessed by comparing with baseline values using the SAQ, patient health questionnaire 9 and Generalized Anxiety Disorder Scale -7. Finally, the volume of contrast used during the procedure and the total cost of medical care covering OMT and the equipment for coronary artery disease therapy from the day of enrollment (first hospitalization) to the last follow-up (rehospitalization) will be evaluated. Perioperative myocardial infarction will be evaluated by assessing CK, CK-MB, and cTNI levels;

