### Sample size calculation

2.7

PASS 15.0 will be utilized to calculate sample size. In the study, 226 individuals are predicted to be recruited in the trial. This sample size was calculated using the optimal efficiency test. The main purpose of this trial is to investigate the effect successfully opening concurrent CTO lesions on cardiac function in patients with MVD. LVEF has been taken into consideration for the calculation of sample size. Previous studies revealed a 6.5% mean difference between the two experimental groups and a 9% standard deviation with respect to LVEF. The optimal boundary value for LVEF was set to 4%.^[21]^ Two-hundred sixteen cases recruited to the study will allow for the use of a 1-tailed test with a significance level (α) set to 0.025, and power (1-β) of 0.90. Ultimately, it is estimated that 240 patients will be randomized, and a 10% loss is expected to occur throughout the 1-year follow-up period.

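### Failed CTO-PCI leaves the primary analysis, but controls whose CTO is opened under section 2.2 have no matching rule, so the per protocol comparison answers neither the strategy question nor the opened-artery question

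*Protocol article*

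**What the plan says.** All references are to the protocol article.

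- **Section 2.2, Treatment groups.** "Patients of the non-CTO PCI group will only have PCI performed on the non-CTO artery". The section then adds that "those with persisting clinical symptoms occurring within one month of OMT will undergo PCI of CTO artery". The expected share of such patients is not given.
- **Section 2.7, Sample size calculation.** "The main purpose of this trial is to investigate the effect successfully opening concurrent CTO lesions on cardiac function in patients with MVD".
- **Section 2.8, Statistical analysis.** In the full analysis set, "all randomized patients will be kept in the treatment group to which they were originally randomized". For the other set, "patients without protocol deviation will be included in the per protocol set". A further rule covers unsuccessful procedures among its members, who "will be included in baseline information analysis rather than in primary analysis if the CTO-PCI fails". A separate rule covers events during follow-up: "Patients will not be included in the primary analysis if the MACEs occur".
- **Section 2.6.2, Secondary endpoints.** The MACE definition includes "target lesion revascularization (PCI or CABG), stroke, heart failure and cardiac rehospitalization within 1, 6, and 12 months post-PCI".

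The article does not say whether a CTO-PCI done under section 2.2 is a protocol deviation, a MACE or neither.

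**The concern.** In the CTO-PCI arm, the result of the procedure decides who contributes to the primary comparison: an artery that stays closed takes the patient out. In the control arm, no stated rule looks at whether the CTO was opened. A control treated as section 2.2 directs has followed the protocol and, on the plain wording, remains in the per protocol comparison under the non-CTO PCI label.

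The failure rule names no arm, which makes this worse if it is read literally. A switched control whose CTO-PCI fails, and whose artery is still closed, would leave, while one whose CTO-PCI succeeds would stay. That is the reverse of what a comparison of opened with unopened arteries needs.

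At stake is the meaning of the LVEF difference. A comparison of strategies keeps failures and switchers where they were randomised. A comparison of opened with unopened arteries needs one definition of treatment received in both arms. The stated rules do neither.

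**Working it through.** **1. The plan's own figure.** With a difference of 4 points, SD 9, one-sided alpha 0.025 and power 0.90 (section 2.7), the t-test calculation gives 107.36, so 108 per arm and 216 in total; 216 / 0.90 = 240 randomised. Both stated figures are reproduced when 4 points is the difference to detect, so 4 points is used below.

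**2. What happens to an opened control under each classification.**

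- *Neither deviation nor MACE:* stays in the per protocol comparison as a control with an open artery. The difference is diluted.
- *MACE* (for example as cardiac rehospitalisation): leaves the primary analysis. Patients chosen by persisting symptoms after randomisation are lost from one arm.
- *Deviation:* leaves the per protocol set, with the same selection.

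**3. Size if switchers stay (illustration).** Assumptions: share c of controls switch (not in the documents); 80% of their procedures succeed (the target in section 2.4.1, borrowed for switchers); opening is worth 4 points; failures are removed from the CTO-PCI arm; removal has no selection effect.

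Difference = 4 × (1 − 0.8c)

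- c = 10% (about 11 of 108): 3.68
- c = 15% (about 16): 3.52
- c = 20% (about 22): 3.36
- c = 30% (about 32): 3.04

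If failed switchers are also removed, the opened share among the remaining controls is 0.8c / (1 − 0.2c). At c = 20% that is 0.16 / 0.96 = 0.167, and the difference is 3.33 instead of 3.36. If every switcher is successfully opened, the difference is 4 × (1 − c) = 3.6, 3.2 and 2.8 at 10%, 20% and 30%. With 108 controls and 86.4 CTO-PCI patients (20% failures removed), power is then 0.79, 0.69 and 0.58, against 0.87 without switching.

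**4. Against the sampling error.** Standard error = 9 × √(1/108 + 1/86.4) = 1.30. The losses in step 3 at 10%, 20% and 30% are 0.32, 0.64 and 0.96 points, or about 0.25, 0.49 and 0.74 of one standard error.

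**5. Size if switchers are removed.** If the removed share c would have had a mean change d points away from that of the other controls, removal shifts the control mean by c × d. The same form applies to failures in the CTO-PCI arm. The documents give no basis for d, so neither size nor sign can be stated.

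**6. What the suggested analyses would return, under the assumptions of step 3 and 80% success in the CTO-PCI arm.** As randomised, the difference is 4 × (0.8 − 0.8c) = 2.88, 2.56 and 2.24 at 10%, 20% and 30%. Dividing by the difference in opened share returns the effect of opening: at 20%, 2.56 / (0.80 − 0.16) = 4.0. The standard error is roughly 9 × √(2/108) / 0.64 = 1.22 / 0.64 = 1.9, against 1.30 in step 4.

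**The case against.** The strongest case against is that the article is only ambiguous here. The term deviation is not defined, and a definition is commonly left to the full protocol or analysis plan. Section 2.2 also limits controls to PCI of the non-CTO artery, so an opened control could be classed as a departure from assigned treatment. The MACE rule may remove some or all switched controls. The dilution at 10% to 20% switching is at most half a standard error, and the full analysis set still keeps everyone as randomised.

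Much of this stands, and it rules out several stronger readings that a reader might infer:

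- *That failed CTO-PCI patients are taken out of the per protocol set.* They stay in it for baseline description and leave the primary analysis.
- *That the control arm of the primary comparison certainly mixes opened and unopened arteries.* This is the plain reading, but the MACE rule or a deviation ruling could remove those controls. It is unclear whether a CTO never treated before counts as a target lesion.
- *That the per protocol set is declared to isolate the effect of opening.* Section 2.7 names that aim, but no section assigns it to a set.
- *That the result could not be interpreted.* The illustrated dilution is too small to support this.

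The objection does not remove the point. The failure and MACE exclusions are stated rules, not missing detail, and each classification of an opened control leaves a distorted comparison: dilution if retained, selection after randomisation if removed.

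**Conclusion.** The point holds as a conflict between stated rules. Section 2.8 selects on procedural result when CTO-PCI fails and has no counterpart for a control's CTO opened under section 2.2. The resulting comparison matches neither the randomised strategies nor the aim in section 2.7.

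If switchers are retained, an assumed 10% to 30% switching turns 4 points into about 3.7 to 3.0. This rests on 80% success in switchers and no selection effect. It is only one component of the error: removing failures or MACE patients may push the estimate in another direction, so the net error cannot be signed. The point deserves correction before analysis, but it does not show that the trial fails.

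**What to change.** 1. Reconcile sections 2.2, 2.6.2 and 2.8 by stating whether a CTO-PCI under section 2.2 is a deviation, a MACE or neither. This leaves the clinical rule itself to the investigators.
2. Base the primary LVEF comparison on the full analysis set, with failed CTO-PCI patients and switched controls kept as randomised, however the switch is classified.
3. Label the per protocol analysis descriptive and apply one treatment-received rule to both arms.
4. For the aim in section 2.7, add a supportive estimate with randomisation as the instrument and a CTO successfully opened before the 12-month CMR as treatment received, defined identically in both arms. This needs the date and procedural result of every CTO-PCI in either arm.

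The cost is wording, a few data fields if they are not already collected, and one more analysis. There are three downsides to state. The instrument-based interval is wider. That estimate also assumes that assignment affects LVEF only through opening, which complications of failed attempts, such as the perforation and infarction listed in section 2.6.3, could violate; it can therefore only be supportive. Finally, if 4 points is the effect of an opened artery and not of the strategy, 80% success alone lowers the as-randomised difference to 3.2 points and power at 108 per arm to 0.74, with further loss from switching.

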**Conclusion::**

The SOS-moral trial will provide data necessary to determine whether to open concurrent CTOs among MVD patients with CMR-detected necrotic myocardial tissue.

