#### PCI procedure

2.4.1

Experienced operators have been designated to ensure that the success rate of CTO-PCI is above 80%. Procedural success is defined as resulting in residual stenosis of <10% with thrombolysis in myocardial infarction grade 3 flow, in the absence of dissection and thrombosis. The use of a DES and specialized devices will be left to the discretion of the operator.

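### Section 2.8 drops failed CTO-PCI patients from the primary analysis, so the primary comparison sets selected successes against essentially unselected controls

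*Protocol article*

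**What the plan says.** Section 2.8 (Statistical analysis) makes three statements that bear on who is analysed.

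- It defines an all-randomised set: "In the full analysis set, all randomized patients will be kept in the treatment group to which they were originally randomized". It does not say that the primary endpoint is analysed in this set.
- It then says: "Patients of the per protocol set will be included in baseline information analysis rather than in primary analysis if the CTO-PCI fails".
- The next sentence adds: "Patients will not be included in the primary analysis if the MACEs occur".

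Section 2.4.1 fixes what counts as success: "Procedural success is defined as resulting in residual stenosis of <10% with thrombolysis in myocardial infarction grade 3 flow", with no dissection or thrombosis. On the expected rate it says: "Experienced operators have been designated to ensure that the success rate of CTO-PCI is above 80" per cent, and section 2.9 repeats this. For the control arm, section 2.2 says: "Patients of the non-CTO PCI group will only have PCI performed on the non-CTO artery". The same section sends patients whose symptoms persist within one month of medical therapy to PCI of the CTO artery.

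The question is stated in two ways. The abstract's conclusion promises data to "determine whether to open concurrent CTOs among MVD patients with CMR-detected necrotic myocardial tissue". Section 2.7 says: "The main purpose of this trial is to investigate the effect successfully opening concurrent CTO lesions on cardiac function", and the Discussion (section 3) also frames the evidence gap in terms of successful opening.

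**The concern.** Whether to open a CTO is decided before anyone knows whether the attempt will succeed. Success depends on the lesion, the patient and the operator, and it is observed after randomisation. Removing failures from the CTO-PCI arm leaves a group selected on that later outcome. The control arm still contains its own would-fail patients, because in most controls the CTO is never attempted and they cannot be identified. The groups compared are then no longer those created by randomisation.

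Two separate consequences follow.

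- **Selection bias.** If patients with hard-to-open lesions have a poorer 12-month LVEF course whatever is done, the exclusion favours CTO-PCI even when opening the vessel does nothing.
- **A different question.** Even without that bias, the result describes patients in whom the procedure worked. It leaves out attempts that ended in dissection or thrombosis, so any loss of LVEF caused by such an attempt disappears from the primary endpoint.

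**Working it through.** **Inputs from the protocol article.** SD 9 LVEF points, boundary value 4 points, prior difference 6.5 points, one-sided alpha 0.025, power 0.90, 216 evaluable, 240 randomised, 10% loss (section 2.7); 1:1 allocation (section 2.1); success above 80% (sections 2.4.1 and 2.9), so failure below 20%. The Introduction gives success above 90% at experienced centres, so 10% failure is used as the second case.

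**Assumed, not in the documents.** The gap d, in LVEF points, by which the 12-month change in would-fail patients is worse than in would-succeed patients regardless of treatment. Range shown: 0 to 8.

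**Step 1: the plan's own figure.** For a difference of 4 and SD 9, n per arm = 2 × (1.960 + 1.282)² × 9² / 4² = 106.4, so 107 per arm or 214 in total. The t-test version gives 108 per arm, 216 in total. Then 216 / 0.90 = 240. The stated 216 and 240 reproduce with 4 points as the detectable difference.

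**Step 2: numbers left under the exclusion.** Each arm has 120 × 0.90 = 108 evaluable. At 20% failure the CTO-PCI arm keeps 108 × 0.8 = 86.4; at 10%, 108 × 0.9 = 97.2. The lost numbers are a minor matter: at 20% failure, power for 4 points is still 86.8%.

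**Step 3: bias with no true effect.** Let m be the mean change in would-succeed patients and f the failure share. The control mean is m − f × d. The CTO-PCI mean after exclusion is m. The expected difference is f × d.

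**Step 4: one-sided type I error.** SE = 9 × √(1/108 + 1/n), where n is the number kept in the CTO-PCI arm. This is 1.30 for n = 86.4 and 1.26 for n = 97.2. Rejection probability = Φ(f × d / SE − 1.96).

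| d (points) | Bias, 20% failure | Type I error | Bias, 10% failure | Type I error |
|---|---|---|---|---|
| 0 | 0 | 2.5% | 0 | 2.5% |
| 3 | 0.6 | 6.7% | 0.3 | 4.3% |
| 5 | 1.0 | 11.7% | 0.5 | 5.9% |
| 8 | 1.6 | 23% | 0.8 | 9.3% |

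**Step 5: effect of success against effect of the strategy.** Suppose there is no prognostic gap and a failed attempt brings no benefit. A 4-point effect in successes is then 0.8 × 4 = 3.2 points for the strategy at 80% success, and 0.9 × 4 = 3.6 at 90%.

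**Step 6: power once failures are kept.** With 108 per arm, SE = 9 × √(2/108) = 1.225 and power = Φ(effect / 1.225 − 1.96).

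- 4 points: 90.4%.
- 3.6 points: 83.6%. For 90% power, 264 evaluable and 294 randomised.
- 3.2 points: 74.3%. For 90% power, 334 evaluable and 372 randomised.
- 6.5 points in successes, diluted to 0.8 × 6.5 = 5.2: 98.9%.

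**The case against.** Five points can be made for the plan.

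- **The exclusion sentence opens with the per protocol set.** It could be read as a rule inside that set, with the full analysis set serving for the main result. But the sentence names the primary analysis, no sentence gives the primary endpoint to the full analysis set, and the MACE sentence that follows has no such limit. If a per protocol rule was meant, the wording still needs correcting.
- **Failure is not confined to one arm.** A reader might infer that the exclusion can only strike the CTO-PCI arm. Section 2.2 does not support this: symptomatic controls may cross over to CTO-PCI, and a failed crossover would also meet the rule. That is a selected subgroup of controls, so the imbalance remains, but it is near-complete and not absolute.
- **The trial is not incapable of answering.** A reader might infer that it cannot say whether to open a CTO. It can, because an all-randomised set is defined. The fault lies in the primary analysis as written.
- **Successful opening may be the intended question.** Sections 2.7 and 3 say so, and the document is inconsistent rather than uniformly about strategy. This does not rescue the rule. Deleting failures from essentially one arm does not estimate the effect of success without bias either, because there is no matching would-succeed control group.
- **The size is uncertain.** The gap d has no source in the documents, 20% failure is a ceiling, and 8 points exceeds the 6.5-point treatment difference in section 2.7. At d = 0 the selection bias vanishes, and if would-fail patients did better it would reverse. The dilution to 3.2 points is also conditional: section 2.4.1 counts residual stenosis of 10% or more as failure, so a partly opened vessel may still bring some benefit.

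The qualifications on arm, capability and size stand. None removes the defect.

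**Conclusion.** The point holds in this form. Section 2.8 states a post-randomisation exclusion from the primary analysis that falls almost entirely on the CTO-PCI arm. This is a rule the protocol fixes, not a detail left to a later plan. The resulting contrast does not answer the abstract's question, and it does not give an unbiased answer to the question in sections 2.7 and 3.

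The size depends on two quantities. The failure share is bounded by the protocol at 20%. The prognostic gap is assumed. Over gaps of 3 to 8 points, one-sided type I error runs from 6.7% to 23% at 20% failure and from 4.3% to 9.3% at 10%, against a nominal 2.5%. With no gap there is no selection bias, but the estimate still describes success rather than the strategy: 4 points against 3.2 to 3.6 if failed attempts bring no benefit. It should be settled before any results are seen, because it governs the primary endpoint.

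**What to change.** 1. In section 2.8, name the full analysis set as the set for the primary endpoint: all randomised patients in their assigned arm, whatever the CTO-PCI result.
2. Delete the CTO-PCI-failure exclusion, or confine it to a supplementary per protocol analysis.
3. Treat the MACE sentence in the same way. Removing only the failure sentence would still not leave all randomised patients in the primary analysis.
4. Align the abstract's conclusion and sections 2.7, 2.8 and 3 on one question.
5. If the effect of successful opening is wanted, report it as a secondary estimate that keeps the randomised comparison, for example a complier-average effect with assignment as the instrument. State its assumptions: that failed attempts have no effect of their own, which the perioperative complications in section 2.6.3 make questionable, and how control crossover under section 2.2 is handled.

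**Cost.** The changes are to wording. No extra visits are needed, since the 12-month assessment is already planned for both arms. A reader might infer that the change is also free in power, and that does not follow. Section 2.7 should say whether 4 points is the effect in successes or of the strategy. If it is the effect in successes and failed attempts bring no benefit, power at 216 evaluable is about 74% at 80% success and 84% at 90%. If the effect in successes is 6.5 points, power stays near 99%.

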#### Primary endpoint

2.6.1

The primary endpoint of this SOS-moral study will be difference in cardiac function observed between baseline and 1-year post-intervention, which will be determined by CMR and transthoracic echocardiography.

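### Leaving every patient with a MACE out of the primary analysis turns the cardiac-function comparison into one among event-free patients, no longer between the randomised groups

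*Protocol article*

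**What the plan says.** The primary endpoint (section 2.6.1) is the "difference in cardiac function observed between baseline and 1-year post-intervention", measured by CMR and echocardiography. Section 2.7 singles out one measure for sizing: "LVEF has been taken into consideration for the calculation of sample size".

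Section 2.8 first defines an as-randomised population: "In the full analysis set, all randomized patients will be kept in the treatment group to which they were originally randomized". It then describes a per-protocol set, says that patients are "included in baseline information analysis rather than in primary analysis if the CTO-PCI fails", and adds: "Patients will not be included in the primary analysis if the MACEs occur". That last sentence has no limit by arm, timing, type of event or analysis set. No sentence in the article names the full analysis set, or any other set, as the primary one.

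Section 2.6.2 makes MACE an outcome of the trial: "Secondary endpoints involve the occurrence of MACEs". The composite covers death, non-fatal infarction and "target lesion revascularization (PCI or CABG), stroke, heart failure and cardiac rehospitalization within 1, 6, and 12 months post-PCI".

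**The concern.** Randomisation makes the two arms comparable as whole groups. Once patients are dropped for something that happens after treatment starts, and that treatment may influence, the remaining groups need not be comparable. MACE fits that description: the trial itself compares it between arms, and two of its components, infarction and heart failure, bear directly on ventricular function.

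The rule can act differently in each arm. A control patient admitted with heart failure leaves the control arm, probably with a poor LVEF. If a procedural infarct counts as MACE, a patient whose LVEF falls because of the CTO procedure leaves the CTO-PCI arm. Either way the primary result answers a question about patients who had no event, a group that cannot be identified at the time of choosing a strategy.

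The rule also removes patients from the analysis, while section 2.7 allows only for a 10% loss over follow-up and names no separate allowance for these exclusions.

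An analysis plan may exist that is not shown here. That does not help: the exclusion is stated in the article, so this is not a detail left for later. A plan that followed it could not also analyse all randomised patients.

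**Working it through.** **1. The plan's own sample size.** Section 2.7 cites "a 6.5% mean difference between the two experimental groups and a 9% standard deviation with respect to LVEF", a boundary value of 4%, one-sided alpha 0.025, power 0.90, 216 evaluable and 240 randomised. A two-sample t-test (noncentral t) with difference 4 and SD 9 needs 108 per arm, so 216; and 216 / 0.90 = 240. Both figures reproduce when 4 points is the difference to detect. Power at 108 per arm is 90.2%.

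**2. Bias from the exclusion.** In one arm, let p be the proportion with a non-fatal MACE and g the mean LVEF change in event-free patients minus that in patients with an event. Then

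- mean of all scanned patients = event-free mean − p·g, so
- event-free contrast − all-patient contrast = p1·g1 − p0·g0 (1 = CTO-PCI, 0 = control).

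The documents give neither p nor g. All values below are assumptions.

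| p1 | p0 | g1 | g0 | Bias (LVEF points) |
|---|---|---|---|---|
| 10% | 10% | 5 | 5 | 0 |
| 20% | 10% | 3 | 3 | +0.3 |
| 20% | 10% | 8 | 8 | +0.8 |
| 10% | 20% | 3 | 3 | −0.3 |
| 10% | 20% | 8 | 8 | −0.8 |
| 15% | 15% | 8 | 4 | 0.15×8 − 0.15×4 = +0.6 |

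A positive value favours CTO-PCI. Against 4 points, 0.3 is 7.5% and 0.8 is 20%. The last row shows that equal MACE rates do not by themselves remove the bias; the gaps must be equal too.

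**3. Effect on the test.** This was simulated with 10,000 trials per setting, 108 per arm before exclusion, no true LVEF effect, and MACE probability rising as LVEF change worsens (logistic slope 0.5 or 1.0 per SD, the same in both arms). Nominal one-sided error is 0.025.

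| MACE control / CTO-PCI | Bias | One-sided rejection in favour of CTO-PCI |
|---|---|---|
| 10% / 10% | about 0 | 0.024 to 0.027 |
| 10% / 20% | +0.41 to +0.75 | 0.047 to 0.085 |
| 20% / 10% | −0.42 to −0.72 | 0.012 to 0.006 |

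**4. Effect on power.** The assumed MACE rate is the same in both arms and comes on top of the 10% loss. Patients per arm = 108 × (1 − rate), rounded down. Noncentrality = 4 / (9·√(2/n)).

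| MACE rate | n per arm | Noncentrality | Power |
|---|---|---|---|
| 0% | 108 | 3.27 | 90.2% |
| 5% | 102 | 3.17 | 88.5% |
| 10% | 97 | 3.10 | 86.9% |
| 20% | 86 | 2.91 | 82.6% |
| 30% | 75 | 2.72 | 77.2% |

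The exclusion of failed CTO-PCI is a separate rule and is left out of these figures.

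**The case against.** The best defence is that the sentence follows two sentences on the per-protocol set and may only continue them. But its subject is patients in general and it refers to the primary analysis. If it was meant for the per-protocol set alone, the text would still not say which population is primary. The sentence needs correcting on either reading.

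Several stronger readings are tempting but not supported:

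- A reader might infer that the rule contradicts the full analysis set. The article defines that set but never assigns the primary analysis to it. The rule departs from the set; it does not contradict it.
- A reader might infer that the rule also removes the patients in whom the strategy does good. It does not: a patient spared an event stays in.
- A reader might take it as settled that a procedural infarct removes a patient from the CTO-PCI arm. Section 2.6.2 counts non-fatal infarction as MACE but mentions perioperative infarction separately, and section 2.6.3 lists perioperative infarction under safety. Whether it triggers the exclusion is open.
- A reader might assume that the bias favours CTO-PCI. The direction cannot be fixed from the documents.

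The power loss depends on reading 4 points as the difference to detect. If the true difference were 6.5 points and the test were plain superiority, 75 per arm would still give about 99% power (noncentrality 6.5 / (9·√(2/75)) = 4.42). It is also not stated what the 10% loss covers, and some deaths may already be counted in it. These points weaken the power argument. They do not touch the bias, which no sample size cures.

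**Conclusion.** The concern stands: following the article as written gives a primary comparison that is not randomised, and nothing elsewhere in the document repairs it. This should be changed before analysis, and before scans after an event are missed.

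The size is uncertain. With an assumed 10-point difference in MACE rates and a common gap of 3 to 8 LVEF points, the bias is 0.3 to 0.8 points in either direction. It is near zero if rates and gaps are the same in both arms, but the plan cannot rely on that when MACE is itself an outcome under comparison. The loss of power is secondary: 1.7 to 13 percentage points for assumed MACE rates of 5% to 30%, on the 4-point reading that reproduces the sample size.

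LVEF stands here for the primary endpoint because it is the sizing variable; the endpoint itself is worded more broadly as cardiac function.

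**What to change.** 1. Delete the sentence that removes patients with a MACE from the primary analysis.
2. State that the primary analysis uses the full analysis set: all randomised patients, by randomised arm.
3. State that the 12-month CMR is obtained and used after any non-fatal MACE.
4. Say within the primary analysis how deaths are handled, since a patient who has died has no 12-month LVEF. One option is an estimand in survivors with deaths reported by arm alongside, plus a sensitivity analysis on a rank-based composite with death as the worst rank, tested by a rank method. The survivor estimand still conditions on a post-randomisation event, but a far narrower one than MACE.
5. Impute only scans that are missing in survivors, not LVEF for patients who have died.
6. Keep a MACE-free analysis, if wanted, as supplementary and labelled as not a randomised comparison.

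The cost is a change of wording, modest programming, and an instruction to sites to keep scanning patients after an event. The 12-month hospital visit is already scheduled in section 2.6, but the article does not say that scanning continues after a MACE, so that instruction has to be explicit.
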